**Table 1 Tab1:** **Dosage plan for clonidine**

Time	Safety	Dosage
Day 1	Systolic BP has to be >120 mmHg before the first loading dose.	75 μg every 3^rd^ hour until maximum 4 doses, (e.g.: at 2, 5, 8 and 11 p.m)
Loading doses	If systolic BP is <100 mmHg, HR <50 beats/min, or if RASS is −3 or less before any of the subsequent loading doses, no more study medication will be given until the planned maintenance dose the next morning.	
	If RASS is −2, the treating physician has to assess if IMP will be given or not	
Day 2-7	If systolic BP is <100 mmHg, HR <50 beats/min, or if RASS is −3 or less just before a planned dose, no study medication will be given until the next planned dose 12 hours later.	75 μg BID, at 8–9 a.m and 8–9 p.m
Maintenance doses		
	If RASS is −2, the treating physician has to assess if IMP will be given or not	

Concentration levels of clonidine known to have clinical effects range from 0.2 to 2.0 ng/ml [50-52]. We are aiming for the lower levels, that is, between 0.3 ng/ml (median trough concentration) and 0.7 ng/ml (maximal concentration), because higher plasma concentration levels increases the risk of adverse events, including hypotension. Nonetheless, lower plasma concentration levels may be insufficient to give a significant effect on our primary endpoint.

To our knowledge, there are no studies of the relationship between plasma concentration of clonidine and delirium. In publications on the effect on delirium of dexmedetomidine, the plasma concentration levels are not reported. Additionally, dexmedetomidine is approximately 8 times more selective (alpha 2 versus alpha 1) than clonidine [28,31], and so pharmacokinetic data on dexmedetomidine cannot be used to estimate effective doses of clonidine. We thus have to extrapolate from pharmacokinetic data on clonidine used for other purposes. We know that clonidine has both sedative and anxiolytic effects, and that these centrally mediated effects are closely related to plasma concentration levels [53,54].

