**Primary**	
Delirium trajectory	MDAS
**Secondary** (also with subanalyses for subsyndromal delirium and hypoactive/hyperactive/mixed delirium)	
Time-to-first delirium resolution	DSM-5
Incidence of “full-scale” delirium	DSM-5
Severity of delirium	MDAS, OSLA
Delirium subtype	MDAS, OSLA, DelApp
Use of “rescue medication”/additional drugs (as other sedatives, analgetics and antipsychotics)	Registration of use of all medication
Length of hospital stay	Registrations
Patient distress	Checklist of Nonverbal Pain Indicators
Cognitive function in follow-up after 4 months	MMSE-NR, Clock drawing test, Ten-words memory test, Trial making test A and B, IQCODE, CDR
Independence in follow-up after 4 months	Barthel ADL, NEADL
Pharmacokinetic response to clonidine	Serum drug concentrations
Pharmacodynamic response to clonidine	BP, HR, ECG, RASS, OSLA, symptoms of bradycardia, orthostatic hypotension or other side-effects
Biomarkers	Blood samples
Institutionalisation	Registrations
Survival	Registrations

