### Study medication

Each capsule (CAPSUGEL) will contain either 75 μg Catapresan (clonidine hydrochloride) or 75 μg placebo, and will be produced and labeled by Kragerø tablettproduksjon A/S. The capsules containing active medication and placebo will look identical. If other medications are indicated for the treatment of delirium, the treating physician will prescribe this as “standard care”.

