### Criteria for patient discontinuation

Patients may be discontinued from study treatment and assessments for several reasons. These include: omission of more than 3 following dosages, voluntary discontinuation by the patient, safety reasons as judged by the study physician or treating physician, or significant non-compliance with the protocol as judged by the study physician. Any patient withdrawn from the study will be included in the statistical intention-to-treat analysis. If possible, a final assessment shall be made (end of study visit) and the reason for discontinuation shall be recorded. Progression of delirium is not a discontinuation criterion, as the trajectories are variable and impossible to predict. Progression of delirium may however make the patient unwilling to further participate. If any of the exclusion criteria appear during the treatment, treatment will be discontinued. (Except changes in blood pressure and heart rate, which will be managed as described in the dosage plan).

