### Statistical analysis

The primary endpoint is the repeated measurements of MDAS over time. Differences in the MDAS trajectories between the treatment groups will be analysed by a mixed linear model. In addition we will, as a secondary endpoint, compare the time to resolution of delirium as measured by DSM-5. The Kaplan Meier method and the logrank test will be applied. In addition a Cox proportional hazards model will be applied to estimate hazard ratios. The additional different secondary endpoints will be analysed by t-tests when variables are continuous and by chi-square tests when variables are categorical. Patient survival will be compared between groups by the logrank test and Cox proportional hazards model.

For the comparison of the MDAS trajectories no adjustment for multiplicity will be applied. If a statistically significant difference between the MDAS trajectories is demonstrated, analyses of secondary endpoints will be performed without any formal adjustment for multiplicity. If any conclusion on efficacy is to be drawn based on a secondary endpoint only, a simple Bonferroni adjustment (dividing the 5% level with the actual number of tests performed) will be applied. If the use of additional antipsychotics differs between treatment groups, the amount calculated as haloperidol equivalents [68] will be included in the statistical model.

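### The rule that adds antipsychotic amount to the model when the arms differ adjusts for a consequence of treatment, so the adjusted contrast is no longer the randomised effect on MDAS

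*Protocol article*

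**What the plan says.** The Statistical analysis section of the protocol article sets the primary analysis: "Differences in the MDAS trajectories between the treatment groups will be analysed by a mixed linear model". The same section ends with the rule at issue: "If the use of additional antipsychotics differs between treatment groups, the amount calculated as haloperidol equivalents [68] will be included in the statistical model". It gives no criterion for a difference in use, does not call the adjusted fit a sensitivity analysis, and does not say that an unadjusted fit stays primary.

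Three other places bear on it:

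- Study medication: "If other medications are indicated for the treatment of delirium, the treating physician will prescribe this" as part of standard care. Antipsychotic use is thus decided after randomisation, by indication.
- Table 2 lists rescue medication among the secondary endpoints, including "additional drugs (as other sedatives, analgetics and antipsychotics". The protocol itself treats antipsychotic use as something clonidine may change.
- Criteria for patient discontinuation: "Any patient withdrawn from the study will be included in the statistical intention-to-treat analysis". The stated principle is intention to treat.

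**The concern.** A covariate that treatment can alter is not a baseline covariate. Antipsychotic amount depends on how delirious the patient has been, which is what MDAS measures, and possibly on clonidine directly: the text following the dosage table says "We know that clonidine has both sedative and anxiolytic effects". Comparing arms at equal antipsychotic amount sets clonidine patients against the milder placebo patients who needed equally little. If clonidine works, part of its effect is removed. If clonidine only calms patients so that fewer antipsychotics are prescribed, the adjustment creates a difference in MDAS that does not exist.

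The trigger makes this worse. The covariate enters when the arms differ on it, which is when its inclusion moves the estimate most.

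The single primary comparison is at stake, and with it the gate to the secondary endpoints: the Statistical analysis section lets them go without multiplicity adjustment once the MDAS comparison is significant.

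**Working it through.** **Inputs from the protocol.** N = 100; SD of MDAS 9; difference 5 (or 3.5); correlation between measurements 0.5 (all from the sample size section). 1:1 allocation, so 50 per arm, is inferred from the 10 and 10 in the Safety review section. The 5% level is taken as two-sided.

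**Plan's own figures.** One time point: SE = 9 × √(2/50) = 1.80; 5/1.80 = 2.78; power = Φ(2.78 − 1.96) ≈ 79%, against the stated approximate 80%. Recovery of 40% vs 65% gives 71.3%, against the stated 71%. Both reproduce. The protocol gives no figure for the antipsychotic adjustment.

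**Assumptions needed.** How strongly antipsychotic amount follows severity, and what counts as a difference between arms (taken as p < 0.05). Neither is in the document, so ranges are shown.

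**Check 1: closed form, confirmed by simulation (5 scores per patient, assumed).** Let U be a patient's underlying severity, with SD √(0.5 × 81) = 6.36. Let antipsychotic amount, in SD units, have within-arm correlation ρ with U. Let δ be the true MDAS difference (negative favours clonidine) and s any shift in antipsychotic amount by another route. Then:

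- arm difference in amount = ρδ/6.36 + s
- within-arm slope of MDAS on amount = 6.36ρ
- adjusted difference = δ − 6.36ρ(ρδ/6.36 + s) = δ(1 − ρ²) − 6.36ρs

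With s = 0:

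| ρ | δ = −5: adjusted | power, rule (unadjusted 94%) | δ = −3.5: adjusted | power, rule (unadjusted 70%) |
|---|---|---|---|---|
| 0.3 | −5 × 0.91 = −4.55 | 93% | −3.19 | 68% |
| 0.5 | −5 × 0.75 = −3.75 | 86% | −2.63 | 61% |
| 0.7 | −5 × 0.51 = −2.55 | 65% | −1.79 | 45% |

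With δ = 0 and clonidine lowering antipsychotic use by another route, the false difference is 6.36ρ|s|, against clonidine. For example, ρ = 0.5 and s = −0.5 give 1.6 points. Type I error of the rule (unadjusted about 5%):

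| ρ | s = −0.25 SD | s = −0.5 SD | s = −0.75 SD |
|---|---|---|---|
| 0.3 | 5% | 9% | 16% |
| 0.5 | 6% | 18% | 41% |
| 0.7 | 7% | 37% | 79% |

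With δ = 0 and s = 0, type I error of the rule is 3.8% to 5.0%.

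**Check 2: day-by-day prescribing.** Seven daily scores; the chance of an antipsychotic on a given day rises with the previous day's MDAS (logit = slope × (MDAS − 18), mean MDAS taken as 18); the covariate is the number of antipsychotic days; true difference 5.

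| Slope per point | Within-arm correlation | Adjusted difference | Power, rule (unadjusted about 95%) |
|---|---|---|---|
| 0.05 | 0.39 | 4.3 | about 94% |
| 0.10 | 0.62 | 3.3 | about 88% |
| 0.25 | 0.83 | 2.0 | about 72% |

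With no MDAS effect but prescribing lowered by 0.7 log-odds in the clonidine arm, type I error is 32% to 62% across these slopes. With neither effect it stays at or below 5%.

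**Check 3: antipsychotics that themselves lower MDAS.** If they lower it by b points per SD of amount, then in the Check 1 model with s = 0 the unadjusted difference is δ(1 − bρ/6.36) and the adjusted one is still δ(1 − ρ²). Adjustment enlarges the estimate only when ρ < b/6.36. With δ = −3.5:

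- b = 1.5, ρ = 0.7: simulated −2.94 unadjusted, −1.80 adjusted
- b = 3, ρ = 0.3: simulated −3.00 unadjusted, −3.18 adjusted

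In neither case does the adjusted fit recover −3.5.

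**The case against.** The best defence is that rescue drugs can mask a benefit: if placebo patients receive more antipsychotics and these work, the unadjusted contrast understates what clonidine does alone. That is probably why the rule was written. It stands to this extent: with a strong drug effect and weak confounding by severity, adjustment moves the estimate up. But total amount is itself driven by severity, so the covariate does not isolate the drug effect, and the Background calls the evidence that antipsychotics work weak.

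The sentence also names no model. It follows text on secondary endpoints, Cox models appear in the same section, and the sample size section describes the primary analysis without this covariate. A reader might infer that the protocol expressly makes the adjusted fit the primary result. It does not; that is the natural reading, not a stated one. An analysis plan could resolve it, but the sentence as written is an instruction, and no unadjusted fit is preserved.

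A reader might also infer that the rule inflates type I error under any null. It does not: inflation needs an effect on antipsychotic use without an effect on MDAS. Sedation makes that plausible, but nothing in the document sizes it.

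Finally, the trial describes itself as exploratory. That limits the consequences but does not make the adjusted contrast the right one.

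**Conclusion.** The concern holds. Followed as written, and read as applying to the primary MDAS model, the rule replaces the randomised comparison with one conditioned on a post-randomisation consequence of treatment, and does so depending on the data.

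Shrinkage of a true benefit is the usual result, not a certain one. Its size depends wholly on how closely prescribing follows severity: slight at the weak end, more than half of a 5-point difference at the strong end. The steepest slope, 0.25 per point, implies an odds ratio of exp(0.25 × 9) ≈ 9.5 per SD of MDAS and should be read as near worst case. A reader might take that end as the expected loss; no figure in the protocol supports doing so.

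The false difference arises only if clonidine changes antipsychotic use by another route. It then goes against clonidine if use falls and in its favour if use rises. At the weakest setting examined, type I error is still about 5%; at the strongest it is 79%.

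The case for change rests on the loss of the randomised contrast, which needs none of these assumed magnitudes.

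**What to change.** Replace the sentence with three statements:

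1. The primary MDAS comparison is by randomised group regardless of rescue medication, without antipsychotic amount as a covariate.
2. Haloperidol equivalents are reported and compared by arm under the rescue-medication endpoint already in Table 2.
3. Any analysis that accounts for rescue antipsychotics is supplementary, has its method and target effect specified in advance, and is run whether or not the arms differ.

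This is a wording change to make before unblinding. It needs no new data and no change to treatment or prescribing. In the simulations, leaving the covariate out keeps type I error at about 5% in every null scenario.

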### Sample size, statistical power and statistical analysis

Based on the expected number of patients fulfilling the inclusion criteria within 36 months a sample size of n = 100 was chosen. Inclusion of 100 patients would lead to a power of only 71% to detect an absolute treatment difference of 25% in proportion recovered according to DSM-% (40% vs 65%). Correspondingly, using MDAS at one single point in time as the response measure would lead to approximately 80% power assuming a standard deviation of 9 and a difference in mean MDAS score of 5. Thus, analyzing treatment efficacy at only one point in time would lead to low power. An analysis of repeated measurements will reduce random variability and thereby increase power. The primary analysis is therefore a mixed linear model taking all MDAS measurements into account.

The expected efficiency gain is difficult to estimate precisely, but assuming a standard deviation of 9 on the MDAS and a correlation between measurements of r = 0.5, the power would be around 95% to detect a mean MDAS difference of 5 or a power of 80% to detect a mean difference of 3.5 between groups.

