### Safety review

A safety review will be done after we have recruited 20 patients (10 placebo and 10 clonidine). Recruitment of the additional 80 patients will be halted until we have made an assessment of the serum concentration levels, pharmacokinetics and -dynamics (the haemodynamic response) in these initial 20 patients. These data will then guide further dosage for the subsequent 80 patients. We are aiming for serum concentration levels between 0.3 and 0.7 ng/ml, but may accept a small number of single measures above this range. Blood samples for serum concentration measurement will be taken 3 hours after the patient has taken the study drug (each time) on day 1 and just before administration of study drug between 0800 and 0900 on day 2. The serum concentration levels and pharmacodynamic responses will be assessed by an independent Data Monitoring Committee. The determination of the further dosage plan will thus be based on both pharmacokinetics/serum concentration levels and the individual patients´ haemodynamic responses. The further dosage plan will be approved by The Norwegian Medicines Agency.

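### The two power figures given for the repeated-measures primary analysis cannot both be right: they imply different standard errors for one design

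*Protocol article*

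**What the plan says.** The section on sample size and power in the protocol article begins with feasibility: given the number of eligible patients expected over 36 months, "a sample size of n = 100 was chosen". It then reports what that number buys.

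- Recovery by DSM-5 criteria, 40% against 65%: "a power of only 71% to detect an absolute treatment difference of 25" percentage points.
- MDAS at one time point: "approximately 80% power assuming a standard deviation of 9 and a difference in mean MDAS score of 5".
- MDAS as repeated measurements, "assuming a standard deviation of 9 on the MDAS and a correlation between measurements of r = 0.5": "around 95% to detect a mean MDAS difference of 5 or a power of 80% to detect a mean difference of 3.5".

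The section calls the gain from repeated measurement hard to pin down, and uses that gain to support the choice of analysis: "The primary analysis is therefore a mixed linear model taking all MDAS measurements into account". It does not give the number of measurements behind the last pair of figures, the form of the correlation, or whether baseline MDAS is a covariate.

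**The concern.** The last pair of figures shares n, SD, correlation and model. Once the standard error of the treatment difference is fixed, power at 5 points determines power at 3.5 points. A fall from about 95% to only 80% over that range looks too shallow.

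The pair is the only quantified sensitivity of the primary analysis. If the 3.5-point figure is the wrong one, the chance of missing a true 3.5-point difference is about 29% rather than 20%. The section on secondary endpoints says that the trial should help to design a later, more definite study, so a wrong detectable difference could carry over into that planning.

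**Working it through.** **Inputs.** N = 100, SD 9 and r = 0.5 come from the sample size section. Two inputs are inferred. Equal allocation (50 per arm) is suggested by the 10/10 split of the first 20 patients in the Safety review section. Two-sided 5% is inferred from the 5% level in the Statistical analysis section and from the fit of the first two power figures below. No dropout is allowed for, as none is stated.

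**Step 1: reproduce the figures that can be reproduced.**

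- Single time point: SE = 9 × √(2/50) = 1.80. Power = Φ(5/1.80 − 1.960) = Φ(0.818) = 79.3%, against approximately 80% stated. One-sided testing would give 87.1%.
- 40% against 65%: the pooled proportion is 0.525, so the SE under the null is √(2 × 0.525 × 0.475/50) = 0.0999. The SE under the alternative is √((0.24 + 0.2275)/50) = 0.0967. Power = Φ((0.25 − 1.960 × 0.0999)/0.0967) = 71.3%, against 71% stated.

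So 50 per arm and two-sided 5% reproduce the other two figures.

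**Step 2: test the pair against itself.** This needs only a common SE.

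- 95% at 5: SE = 5/(1.960 + 1.645) = 1.387.
- 80% at 3.5: SE = 3.5/(1.960 + 0.842) = 1.249.
- Ratio of variances: (1.387/1.249)² = 1.23.
- With SE 1.387, power at 3.5 = Φ(3.5/1.387 − 1.960) = 71.3%. The difference with 80% power is 1.387 × 2.802 = 3.89.
- With SE 1.249, power at 5 = Φ(5/1.249 − 1.960) = 97.9%.
- Allowing as much as 97% at 5 still gives only 76.7% at 3.5.
- One-sided testing does not help: 95% at 5 then implies 74.5% at 3.5.

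**Step 3: see which calculations yield either figure.** Write SE = 1.80 × √f, where f is the variance of the analysed mean relative to one measurement, and k is the number of post-baseline measurements. The values of k are assumed.

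- Constant correlation, no baseline covariate: f = (1 + (k − 1)r)/k.
- The same with baseline MDAS as covariate: f = (1 + (k − 1)r)/k − r².
- Correlation decaying with lag (AR(1), 0.5 at lag one), simple mean.

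| Structure | k | f | Power at 5 | Power at 3.5 | Difference with 80% power |
|---|---|---|---|---|---|
| Constant r, no baseline covariate | 5 | 0.600 | 94.8% | 70.9% | 3.91 |
| | 7 | 0.571 | 95.7% | 73.0% | 3.81 |
| | 14 | 0.536 | 96.7% | 75.7% | 3.69 |
| | no limit | 0.500 | 97.5% | 78.5% | 3.57 |
| Constant r, baseline covariate | 2 | 0.500 | 97.5% | 78.5% | 3.57 |
| | 3 | 0.417 | 99.0% | 85.4% | 3.26 |
| | 7 | 0.321 | 99.8% | 92.9% | 2.86 |
| AR(1) | 5 | 0.445 | 98.6% | 83.0% | 3.36 |

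No row gives the stated pair. Rows near 95% at 5 have 71% to 73% at 3.5. Rows that reach 80% at 3.5 have about 99% at 5.

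**The case against.** The best defence is that the section is openly approximate. It hedges the 95%, says that the efficiency gain is uncertain, and rounds 79.3% to about 80% elsewhere. The nearest consistent pair in the table is 97.5% and 78.5%, which is 2.5 and 1.5 points from the stated figures. This softens the point but does not remove it. Uncertainty about the gain changes the standard error, and so moves both powers together; it cannot give one analysis two standard errors. The nearest pair also needs either unlimited unadjusted measurements or exactly two post-baseline measurements with baseline adjustment, and neither matches daily MDAS.

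Three further objections stand, and each limits how far the point can go.

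- A reader might infer that 80% power at 3.5 points is out of reach. That holds only for constant correlation without a baseline covariate, where the ceiling is 78.5%, just 1.5 points short. The article names a mixed linear model but fixes neither the correlation structure nor the role of baseline. With baseline adjustment, three post-baseline measurements already exceed 80%.
- A reader might infer that the sample size rests on the faulty pair. The section says that it came from expected recruitment.
- Number of measurements, correlation structure and baseline handling are commonly left to the full protocol or analysis plan. Their absence from the article is not itself an error.

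**Conclusion.** The point holds as an internal inconsistency in the stated power of the primary analysis. Either power at 3.5 is about 71% (80% power applying to about 3.9 points), or power at 5 is about 98%. This conclusion rests on a common standard error and a two-sided 5% test, and it persists if the test is one-sided. It needs no assumption about k, the correlation structure or baseline adjustment.

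Which figure is wrong is not settled. Unadjusted constant correlation with 5 to 7 measurements reproduces the 95% and fits a treatment period of at most 7 days, which makes the 3.5-point figure the likelier slip, but that number of measurements is an assumption. It would therefore go too far to conclude that the trial has only about 70% power at 3.5 points: over the structures left open, 3 to 7 measurements give roughly 66% to 93%.

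The weight is moderate or minor. Neither the sample size nor the analysis model changes; what needs correcting is the stated sensitivity.

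**What to change.** Restate both power figures from one calculation, and give beside them the number of measurements, the correlation structure and the handling of baseline MDAS used.

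If unadjusted measurements with constant correlation 0.5 and 5 to 7 assessments were meant, the sentence would give about 95% for a difference of 5 and about 71% to 73% for 3.5, with 80% power for about 3.8 to 3.9. If a baseline-adjusted model was meant, both figures should come from that model. With three post-baseline measurements, for example, they would be about 99% at 5 and 85% at 3.5.

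The cost is a change of text. Under the first option the stated detectable difference becomes slightly less favourable. The sample size of 100 stays as it is.
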